### **7.2 Exclusion Criteria**

A subject will not be eligible for inclusion in this study if any of the following criteria apply:

1. Treatment with any of the following:
  - a. Previously received treatment with tyrosine kinase inhibitors against EGFR (such as erlotinib, gefitinib, icotinib, afatinib, osimertinib, and aumolertinib);
  - b. The patient has undergone major surgery (such as craniotomy, thoracotomy, or laparotomy) within 4 weeks before the first dose of the investigational medicinal product, or undergone minor traumatic surgery (biopsy, bronchoscopy, and thoracic drainage) within 7 days before the first dose of the investigational medicinal product. Major surgeries are defined as Grade 3 and Grade 4 surgeries specified in the "Administrative Measures for Clinical Application of Medical Technology" implemented from Nov. 1, 2018 in Appendix H;
  - c. Patients who have received local radiotherapy within 2 weeks before the first dose of the investigational medicinal product; patients who have received more than 30% of bone marrow irradiation (see Appendix I for the calculated area of bone marrow) or extensive radiotherapy within 4 weeks before the first dose of the investigational medicinal product; patients who have received whole brain radiotherapy for this disease before enrollment;
  - d. Recurrence within 6 months after adjuvant or neoadjuvant treatment for early lung cancer; if there is both neoadjuvant therapy and adjuvant therapy, the adjuvant treatment time will be used for calculation;
  - e. Within 14 days before the first dose of the investigational medicinal product, traditional Chinese medicines and their preparations with anti-tumor effect or adjuvant anti-tumor effect have been used (see Appendix E for the list of drugs);
  - f. Presence of pleural/abdominal effusion requiring clinical intervention (patients who do not require drainage of the effusion or are stable for more than 2 weeks after drainage of the effusion are eligible); presence of pericardial effusion (patients with small amount of pericardial effusion who are stable for 2 weeks or more are eligible). If anti-tumor drugs are used locally (e.g., via intrapleural infusion) during drainage, patients are only eligible with a washout of at least 5 half-lives or 21 days (whichever is shorter) prior to the first dose of study treatment;
  - g. Previously treated with drugs that are strong inhibitors or strong inducers of CYP3A4, or treated with CYP3A4 sensitive substrate drugs with a narrow therapeutic window, within 7 days prior to the first dose of investigational medicinal product; or requiring to continue the treatment with these drugs during the study (see Appendix E for the list of these drugs);
  - h. Receiving drugs known to prolong the QT interval or that may cause torsade de pointes, or requiring to continue the treatment with these drugs during the study (see Appendix E for the list of drugs and washout times);
  - i. Having participated in another clinical trial within 4 weeks or been still within 5 half-lives of the investigational medicinal product in another clinical trial before the first dose of this investigational medicinal product, whichever is longer (except for screening failure).
2. Histologically or cytologically confirmed mixed SCLC and mixed NSCLC, large cell neuroendocrine carcinoma and sarcomatoid carcinoma.
3. At the beginning of study treatment, those with residual toxicity from prior anti-tumor treatment greater than CTCAE Grade 1 that cannot be alleviated, with the exception of hair loss and Grade 2 neurotoxicity from prior anti-tumor treatment. History of intracranial hemorrhage not related to tumor.
4. History of other primary malignant tumors, except for the following:
  - a. Radically treated malignancies that have been inactive for  $\geq 5$  years prior to study enrollment and have a very low risk of recurrence;
  - b. Adequately treated non-melanoma skin cancer or lentigo maligna without evidence of disease recurrence;
  - c. Adequately treated carcinoma *in situ* without evidence of disease recurrence.
5. Diagnosis of meningeal metastasis through clinical symptoms or imaging or cerebrospinal fluid, or brain parenchymal metastasis combined with meningeal metastasis.
6. Patients who are allergic to MRI contrast agent gadolinium or who cannot tolerate MRI examinations (such as patients with pacemakers or metals in the body).
7. Any serious or poorly controlled systemic disease, such as poorly controlled hypertension, active bleeding diathesis, or active infection, as judged by the investigator. There is no need to check for chronic diseases.
8. Serious gastrointestinal dysfunction that may affect drug intake, transport, or absorption, such as inability to take oral drugs, uncontrollable nausea or vomiting, extensive gastrointestinal resection history, uncured recurrent diarrhea, atrophic gastritis, uncured gastric diseases requiring long-term use of acid-reducing proton pump inhibitors, Crohn's disease, ulcerative colitis, etc.
9. Hepatic encephalopathy, hepatorenal syndrome, or cirrhosis.

10. Any of the following cardiac findings:
  - a. Mean QT interval corrected by Fridericia (QTcF) > 470 msec from 3 repeated measurements of electrocardiogram (ECG) at rest;
  - b. Any clinically significant abnormalities in rhythm, conduction, or ECG morphology determined by the investigator (e.g., complete left bundle branch block, third-degree atrioventricular block, second-degree atrioventricular block, and PR interval > 250 msec), as indicated by ECG at rest;
  - c. Presence of any factor that increases the risk of QTc prolongation or arrhythmic events, such as cardiac failure, hypokalemia, congenital long QT syndrome, family history of long QT syndrome, or unexplained sudden death of immediate family members under 40 years of age, or any concomitant medications known to prolong QT interval;
  - d. Left ventricular ejection fraction (LVEF) < 50%.
11. Insufficient bone marrow reserve or organ function, meeting any of the following laboratory test limits (no corrective treatment within 1 week before blood collection for laboratory tests):
  - a. Absolute neutrophil count <  $1.5 \times 10^9/L$ ;
  - b. Platelet count <  $100 \times 10^9/L$ ;
  - c. Hemoglobin < 90 g/L (< 9 g/dL);
  - d. Alanine aminotransferase >  $2.5 \times$  upper limit of normal (ULN) in the absence of demonstrable liver metastases; alanine aminotransferase >  $5 \times$  ULN in the presence of liver metastases;
  - e. Aspartate aminotransferase >  $2.5 \times$  ULN in the absence of demonstrable liver metastases; aspartate aminotransferase >  $5 \times$  ULN in the presence of liver metastases;
  - f. Total bilirubin >  $1.5 \times$  ULN in the absence of demonstrable liver metastases, or total bilirubin >  $3 \times$  ULN in the presence of Gilbert's syndrome (unconjugated hyperbilirubinemia) or liver metastases;
  - g. Creatinine >  $1.5 \times$  ULN and creatinine clearance < 50 mL/min (calculated by Cockcroft-Gault formula); creatinine clearance should be determined only when creatinine is >  $1.5 \times$  ULN;
  - h. Serum albumin (ALB) < 28 g/L;
12. Female subjects who are pregnant and lactating or plan to become pregnant during the study period.
13. History of interstitial lung disease, drug-induced interstitial lung disease, radiation pneumonitis requiring steroid therapy, or any evidence of clinically active interstitial lung disease.
14. History of hypersensitivity to any active or inactive ingredients of aumolertinib or drugs of similar chemical structure or the same class as aumolertinib.
15. Any severe or uncontrolled ocular diseases (particularly severe dry eye syndrome, keratoconjunctivitis sicca, severe exposure keratitis, or other conditions that may increase the risk of epithelial damage) that may increase the safety risks of patients as judged by the physician; or patients who have any eye disorders that require surgical treatment or are expected to require surgical treatment during the study period.
16. Patients who may have poor compliance with the procedures and requirements of the study as judged by the investigator, such as patients who have a clear history of neurological or mental disorders (including epilepsy or dementia), or patients who are currently suffering from mental disorders.
17. Patients with any conditions that may jeopardize patient safety or interfere with study assessments as judged by the investigator.

### 7.3 Recruitment and Screening Number

Prior to screening, each subject recruited will be assigned a screening number in the order of time signing the informed consent form. Once assigned to a subject, the screening number can no longer be reused. If a subject is screened again, a new screening number will be assigned.

Patients, who are not enrolled because they do not meet the inclusion criteria or they meet any of the exclusion criteria after they sign the informed consent form, are considered "screen failures". For patients who fail screening, the active collection of patient information will end when the screen failure status is confirmed. For subjects for whom "screen failure" is confirmed, the screening process will not be initiated anew, unless any of the following conditions are met:

Condition 1: Due to a revision to the study protocol, the patient meets the eligibility criteria for participating in the clinical study.

Condition 2: Due to a change in the status of the patient, the eligibility criteria, which the patient previously failed to meet, will no longer cause the patient to fail screening once again.

When being re-screened, the patient must sign a new informed consent form and will be assigned a new screening number. However, the patient will be re-screened once only. If a previous test has been conducted beyond the protocol-defined time window, the test needs to be repeated. Echocardiogram and per-protocol tumor imaging examinations performed within 28 days prior to randomization need not be conducted anew.

#### 7.4 Enrollment Status

This is a prospective, single-arm, open-label, multi-center clinical trial. It will not involve randomization, and study sites will compete to enroll subjects in the treatment group (aumolertinib 165 mg).

#### 7.5 Procedures for Managing Wrongly Enrolled Subjects

Subjects not meeting the eligibility criteria of the study should not participate in this study. If subjects not meeting the eligibility criteria are enrolled, study treatment should not be provided. If treatment has been started, the investigator should immediately perform a comprehensive assessment and decide whether to discontinue the treatment based on the assessment results. If treatment has been started for a subject not meeting the eligibility criteria, the subject should be withdrawn from the study. This process must be fully documented in the medical record.

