### **7.8 Treatment Discontinuation and Withdrawal from Study**

#### **7.8.1 Treatment discontinuation**

Treatment discontinuation means that the subject no longer receives the study treatment due to the following reasons after the start of study treatment, but is not withdrawn from the study and will complete subsequent follow-ups as scheduled.

1. Progressive disease (refer to 2 in case of free medication)
2. Disease progression after free medication
3. Adverse event
4. Poor compliance

5. Major protocol violation
  6. Patients are no longer eligible to continue with the study treatment as believed by the investigator or funder (e.g., psychiatric disorders or social status that may interfere with subject's rights, safety, cooperation, and participation in this study)
  7. Patients request for treatment discontinuation but agree to continue to be followed up
  8. Patients withdraw the informed consent
  9. Loss to follow-up
  10. Pregnancy
  11. Study termination or site closure
  12. Patients who develop corneal ulcer or interstitial pneumonia should permanently discontinue the treatment
- Every effort should be made to obtain information of patients who discontinue study treatment, including information concerning EOT follow-up and the safety follow-up thereafter. The primary reasons for study treatment discontinuation should be documented on the corresponding eCRF. A patient's request for withdrawal from the study at the same time must be documented in the source documents, with the investigator's signature affixed. In addition, patients who discontinue study treatment due to reasons other than PD should undergo tumor assessments as scheduled until documented PD, unless the patient withdraws from the study due to any of the reasons described in 7.8.2.

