### 9.1.3.5 Survival follow-up

For patients who have discontinued the study treatment, the patient or their family must be contacted once every 12 weeks from the time of treatment discontinuation to obtain survival information until their withdrawal from the study (withdrawal of informed consent, study termination or site closure, loss to follow-up, or death). In addition, details of subsequent anti-tumor treatment regimens and unresolved AEs must be collected, regardless of the date of last contact. The procedures include the following:

- Follow-up once every 12 weeks to document the details of subsequent anti-tumor treatments
- Follow-up once every 12 weeks to record subsequent response/progression data
- Follow-up once every 12 weeks to document the survival status

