#### 11.4.2 Dose modifications associated with adverse events

If a subject experiences any toxicity of CTCAE Grade  $\geq 3$  and/or any toxicity (any grade) deemed unacceptable by the investigator, which is judged by the investigator to be treatment-related, the study treatment should be interrupted, and supportive care should be provided as needed in accordance with local practices/guidelines. If the toxicity is relieved or returns to  $\leq$  CTCAE Grade 1–2 within 3 weeks after onset, the IMP at the original dose or dose reduction therapy 1 in Table 7 may be given again. If the original dose is resumed, the subject should be closely monitored for 3 days; if the same toxic effect occurs within 3 days, dose reduction therapy 1 should be considered. Decisions should be made in agreement between the investigator and the sponsor.

If the toxicity does not recover to  $\leq$  CTCAE Grade 1–2 within 3 weeks after onset, dose reduction therapy 2 should be considered. If the toxicity still does not recover to  $\leq$  CTCAE Grade 1–2 within 3 weeks or the same toxic effect

occurs within 3 days, the subject should be withdrawn from the study and should be followed up until the toxicity is recovered.

"Treatment-related" herein refers to definitely related, possibly related, and indeterminable, not including unlikely related and not related. Specific dose modification principles are presented in Table 10.

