| At any time, if 55 mg is still intolerable (occurrence of Grade $\geq 3$ adverse reactions), permanent discontinuation of study treatment is recommended. |  |                                                                                           |

Note: The severity mentioned above is graded according to the National Cancer Institute - Common Terminology Criteria for Adverse Events Version 5.0 (NCI-CTCAE 5.0). \* If the study treatment is interrupted for more than 3 weeks and the resumption criteria are not met, the study treatment should be permanently discontinued. # Muscular symptoms (including but not limited to): muscle pain, muscle tenderness, muscle twitching, or muscle weakness. When several AEs occur simultaneously, the dose should be modified according to the most severe AE; once the dose is reduced, it cannot be returned to the previous level. Subjects who discontinue treatment should be observed until the resolution of toxicity; dose interruption does not affect scheduled tumor evaluation. The above decisions should be made in agreement between the investigator and the funder.

For certain patients, if the investigator decides to adopt measures such as continuing treatment without interruption, interrupting treatment, modifying the dose, or permanently discontinuing the study treatment, not in accordance with the dose modification provisions of this section, but based on the benefit/risk considerations, agreement should be reached with the funder.

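### Section 7.5 contradicts itself on dosed ineligible subjects, and read literally it could end RECIST scans for patients who stay in the FAS

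*Protocol*

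**What the plan says.** Section 7.5 first bars ineligible subjects from the study and from study treatment. For one who has nevertheless been dosed, "the investigator should immediately perform a comprehensive assessment and decide whether to discontinue the treatment based on the assessment results". The next instruction is: "If treatment has been started for a subject not meeting the eligibility criteria, the subject should be withdrawn from the study". Its only condition, beyond ineligibility, is that dosing has begun.

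Elsewhere the protocol separates two states:

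- **Treatment discontinuation (7.8.1).** The subject stops drug "but is not withdrawn from the study and will complete subsequent follow-ups as scheduled". Patients who stop for reasons other than progression are scanned until progression "unless the patient withdraws from the study due to any of the reasons described in 7.8.2". The listed reasons for discontinuation include "Major protocol violation", which is not defined further.
- **Withdrawal from the study (7.8.2).** The section opens with voluntary withdrawal and gives an open-ended list: consent withdrawn, study or site closed, lost to follow-up, death. Ineligibility is not named. After withdrawal, survival status may be sought from public sources.

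On the analysis side, 12.4.1 puts every patient with at least one dose in the FAS, with no exclusion for ineligibility, and bases the results mainly on that set. Section 12.1.2 wants imaging collected until RECIST progression even after drug stops or another therapy starts. It censors event-free patients at their last RECIST assessment.

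**The concern.** There are two problems.

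First, the two instructions in 7.5 cannot both be followed when the investigator decides that treatment should continue. This is an instruction to sites about conduct, so an analysis plan cannot settle it. About 20 sites are planned, and they may settle it differently.

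Second, the word chosen is the one that 7.8.1 uses for the state it contrasts with stopping drug and staying in follow-up. A site taking 7.5 at its word could stop scheduled scans in a patient who still counts in the primary analysis. If that patient has had no event, the 12.1.2 rule censors them because of a protocol instruction. This is avoidable, and it may be informative if ineligible patients differ in prognosis. Scans that were never done cannot be recovered at analysis.

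**Working it through.** **Reading the text**

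1. *Contradiction.* The investigator's decision in 7.5 can go either way, while the withdrawal instruction applies whichever way it goes. Reading withdrawal as withdrawal from treatment does not help, because a mandatory stop still overrides the decision.
2. *What withdrawal means.* Sections 7.8.1 and 7.8.2 treat leaving the study and stopping drug as different states. Other sections blur them. Section 11.4.2 says that for unresolved or recurrent toxicity "the subject should be withdrawn from the study and should be followed up until the toxicity is recovered", whereas the note to Table 10 says that after a long interruption in which "the resumption criteria are not met, the study treatment should be permanently discontinued". The safety endpoints in 5.2.2 and the adverse event tables in 12.4.3.1 count withdrawals due to adverse events, yet an adverse event is a 7.8.1 reason for stopping drug and is not listed in 7.8.2. The text does not settle which meaning 7.5 intends.
3. *Consequence if read literally.* Scans could stop, while the patient stays in the FAS (12.4.1) and the 12.1.2 imaging principle is not met.

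**Size, for illustration only**

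The protocol gives no figure to reproduce here. It plans 63 patients (5.3). Everything else below is an assumption: k = 1, 3 or 6 dosed ineligible subjects, a 12-month PFS rate of 60% in the others, and a rate r in the affected.

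*Censored at once.* Kaplan-Meier then estimates 60%. The rate had all been observed is [(63 − k) × 0.60 + k × r] / 63.

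| k | r | Fully observed rate | Kaplan-Meier minus observed |
|---|---|---|---|
| 1 | 40% | 37.6/63 = 59.68% | +0.32 points |
| 3 | 40% | 37.2/63 = 59.05% | +0.95 |
| 6 | 40% | 36.6/63 = 58.10% | +1.90 |
| 6 | 0% | 34.2/63 = 54.29% | +5.71 |
| 6 | 100% | 40.2/63 = 63.81% | −3.81 |

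*Withdrawn at month 3, constant hazards, r = 40%.* The large-sample Kaplan-Meier value is {[(63 − k) × 0.6^0.25 + k × 0.4^0.25] / 63} × 0.6^0.75.

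- k = 1: 59.91%, a difference of +0.23 points
- k = 3: 59.72%, +0.68
- k = 6: 59.45%, +1.35

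*Scale.* The standard error of a 60% rate with 63 patients is √(0.6 × 0.4 / 63) = 6.17 points. At r = 40% with immediate censoring, the difference is 0.32/6.17 = 5% to 1.90/6.17 = 31% of one standard error.

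These differences are measured against the all-dosed rate, which is what the FAS targets. Against a rate in eligible patients only, immediate censoring introduces none.

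**The case against.** The best defence is that 7.5 is clumsy wording that means stopping drug. Ineligibility is not a named reason in 7.8.2, which opens with voluntary withdrawal. Sections 6.1, 9.1.3.3 and 12.1.2 and the Appendix B notes all continue scans after drug stops, with no exception for ineligible subjects. Withdrawal is used loosely in several places, and "Major protocol violation" in 7.8.1 already offers a route that keeps follow-up going. All of this stands. It shows that ending the scans is a possible literal reading, not an established intention. It does not remove the contradiction, and it does not tell a site which reading to apply.

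A reader might also infer that survival contact ends, because 9.1.3.5 requires contact "to obtain survival information until their withdrawal from the study". The document does not support this well. The parenthesis that follows spells out what withdrawal covers there: consent withdrawn, study or site closed, loss to follow-up, or death. That list is closed and omits ineligibility.

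Finally, a reader might infer that the primary result is at risk. Nothing in the document shows this. Section 7.5 bars dosing once ineligibility is known, 14.2 allows no exemptions from the criteria, and the design enrols 63 for 49 required to allow for losses. Public sources may also reveal some deaths, although under 12.1.2 a death after two or more missed visits is still censored at the last RECIST assessment.

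**Conclusion.** The concern holds in a limited form. Section 7.5 contradicts itself, and its wording leaves open a reading under which scans end for patients who remain in the primary analysis, against the imaging principle of 12.1.2. That scans must end is not established, and that survival contact ends is not well supported.

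The number affected is unknown and should be small, so any bias in the 12-month PFS rate is probably minor: under the assumed 1 to 6 subjects with a 40% rate, 0.2 to 1.9 points across the two censoring times. The direction depends on how the affected patients would have fared. By itself this does not threaten the primary conclusion. It is worth correcting because the correction is cheap and missing scans cannot be replaced later.

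**What to change.** Replace the last instruction on dosed ineligible subjects in 7.5 with:

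> If the investigator decides to discontinue treatment, the case is recorded as treatment discontinuation under 7.8.1 (major protocol violation). Whether or not treatment is stopped, the subject remains in the study, and RECIST assessments until PD (where feasible) and survival follow-up continue as scheduled unless one of the reasons listed in 7.8.2 applies.

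This keeps the investigator's decision, uses a category the protocol already has, and brings 7.5 into line with 12.1.2 and 12.4.1. The words *where feasible* cover subjects whose ineligibility itself prevents assessment, such as no measurable lesion or intolerance of MRI. The cost is a short wording change in 7.5 and a few already scheduled scans in a handful of patients.
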